### 2.5. Exclusion Criteria

The exclusion criteria are as follows: two or more lesions in the pancreas suspected of pancreatic cancer; psychosis or psychiatric symptoms that interfere with daily life and make study participation difficult; and enrollment in the study deemed as inappropriate by a physician.

### 2.6. Trial Examination Procedures

Participants undergo EUS performed by a physician who has performed at least 100 cases of EUS–TA as a primary physician. Pancreatic primary and metastatic lesions are characterized, and the maximum lesion diameter is measured in B-mode, followed by confirmation that there are no intervening vessels in the puncture route in Doppler mode. EUS–TA is typically performed using a TopGain 19G needle (SonoTip TopGain; Medi-Globe, Achenmuhle, Germany). Negative pressure is applied using suction with a 20 mL syringe or the slow-pull method, and approximately 20 actuations per pass are performed. If possible, the fanning technique is performed during actuation, but it is not mandatory. When a lesion cannot be identified or the puncture line is technically difficult, a change in the puncture needle or physician is considered. If the puncture remains difficult, it is not forced, and the patient is considered a technical failure. If both primary and metastatic lesions are difficult to puncture, alternative biopsies, such as percutaneous biopsies, are considered. Changing the puncture needle for each lesion is not mandatory, but if the needle deteriorates, it is acceptable to use a new needle as needed. It is not specified whether primary or metastatic lesions should be punctured first, but the puncture is basically performed alternately on the primary and metastatic lesions.

For both primary and metastatic lesions, obtained specimens are placed in shale, and a portion of the specimen is cut and considered for rapid on-site evaluation (ROSE). However, ROSE is not mandatory. When ROSE is performed, the remaining specimens are not included in the study because of the small number of specimens. If malignant cells are not confirmed by ROSE, changes in the puncture site, target, and needle are considered; however, a diagnosis of malignancy may be made by histological examination in some cases. Therefore, even if malignant cells cannot be confirmed using ROSE, additional puncturing, without changing the site or puncture method, is considered acceptable. All collected specimens, including residual specimens after ROSE, are individually preserved in formalin bottles for histological evaluation.

The procedure is terminated once two specimens each are obtained from primary and metastatic lesions, after confirming by EUS and endoscopy that there are no findings suggestive of hemorrhage. If bleeding is suspected, endoscopic hemostasis or endovascular treatment will be considered.

Specimens obtained by EUS–TA are thinly sliced after formalin fixation and stained with hematoxylin and eosin. Specimens, excluding those from the ROSE session, are checked to determine whether they meet NOP analysis criteria. The sample volume required for NOP analysis is five 10 μm thick sections, with tumor cellularity of ≥20% and total DNA content of ≥200 ng per slide. A tissue area of approximately 16 mm^2^ per slide is recommended; however, a tissue area of 4 mm^2^ or more yields > 200 ng of total DNA. Therefore, we consider specimens with tumor cellularity of ≥20% and a tissue area of ≥4 mm^2^ as successfully meeting NOP analysis criteria. The pathological evaluation is performed by two pathologists, and any discrepancies in the measurements are resolved by discussion. In this evaluation, tumor cellularity is evaluated at five levels (>80%, 60–80%, 40–60%, 20–40%, and <20%), and tissue area is evaluated at four levels (≥25, 16–25, 4–16, and <4 mm^2^).

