## 3. Discussion

This study will play an important role in determining the target of EUS–TA in pancreatic cancer with distant metastases when CGP analysis is considered. However, there are several limitations. First, the study will not randomize the initial lesion to be punctured and will allow for the same needle to be used to puncture the primary and metastatic lesions, which may have an impact on EUS–TA as the needle tip gradually deteriorates over time, making specimen collection more difficult. However, the primary and metastatic lesions will be punctured alternately after the first lesion is punctured. Changing the puncture needle at the discretion of the physician when they sense needle deterioration will be allowed. These make this the least confounding factor.

The second is the EUS–TA method. The usefulness of wet suction has been reported in recent years [33,34,35,36,37,38,39,40,41,42,43], with better quality specimens obtained compared with those obtained by dry suction. However, in the meta-analysis, the specimen adequacy rate was similar to the slow-pull method and the risk ratio was 1.02 (0.98–1.07) [36]. Moreover, there is no report to date that wet suction is superior to dry suction or the slow-pull method in terms of specimen volume when genomic testing is taken into consideration. In terms of specimen volume with a view of CGP analysis, whether wet or dry suction is better may be an issue for future studies. The primary endpoint of this study is the comparison of the rate of primary and metastatic lesions that met the criteria of the NOP analysis, and as long as the same slow-pull method of negative pressure is applied to both groups, the fact that wet suction is not applied will not affect the primary endpoint.

Finally, double blinding is not possible. The physician naturally knows whether to puncture the primary lesion or the metastatic lesion, which can be a confounding factor. However, despite these limitations, there have been few reports on whether primary lesions or metastatic lesions are more appropriate for collecting specimens for CGP analysis, and this study may provide significant evidence.

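### The lesion comparison is open to order and technique confounding: the starting lesion is left open, alternation does not cancel needle wear, and suction need not match within a patient

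*Protocol article*

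**What the plan says.** **Order and needle.** Section 2.6 of the protocol article says: "It is not specified whether primary or metastatic lesions should be punctured first, but the puncture is basically performed alternately". On the needle it says: "Changing the puncture needle for each lesion is not mandatory, but if the needle deteriorates, it is acceptable to use a new needle". Section 2.6 ends the procedure once each lesion has yielded two specimens, so the usual sequence is four passes.

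The Discussion lists this as its first limitation: "the study will not randomize the initial lesion to be punctured and will allow for the same needle to be used". It gives the mechanism and its direction: "the needle tip gradually deteriorates over time, making specimen collection more difficult". It then relies on two safeguards, alternation after the first puncture and a needle change when the physician senses wear, and concludes that together they leave little confounding. The last limitation concedes that the physician knows which lesion is being punctured.

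**Technique.** Section 2.6 says: "Negative pressure is applied using suction with a 20 mL syringe or the slow-pull method". It states no rule that both lesions of a patient receive the same method. In defending the absence of wet suction, the Discussion says that the primary endpoint is unaffected "as long as the same slow-pull method of negative pressure is applied to both groups". Two other elements may also vary between the lesions: "If possible, the fanning technique is performed during actuation, but it is not mandatory", and when a lesion cannot be identified or the puncture line is difficult, "a change in the puncture needle or physician is considered".

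**Analysis.** Section 2.7 compares the two proportions with Fisher's exact test, which takes no account of order or technique.

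**The concern.** Section 2.2 calls the trial self-controlled. The strength of such a design is that, within a patient, only the lesion differs. That holds only if pass position, needle condition and technique are equal for the two lesions or balanced between them. Here an unblinded physician works without a stated order, so nothing prevents one lesion from going first in most patients. If wear lowers yield, as the Discussion accepts, part of any observed difference would then be a position effect. With a nearly constant order, no analysis could separate the two.

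The stakes are practical. The Conclusions intend a higher metastatic proportion to support recommending metastatic lesions as the target, and possibly to change the standard. Bias in one direction could hide a real advantage, and in the other could create one.

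**Working it through.** **1. The plan's own figure.** Inputs from section 2.7: 70% metastatic, 45% primary, one-sided 0.05, 80% power, Fisher's exact test, 56 patients. Exact enumeration, treating the lesions as two independent groups as the stated test does, gives power 0.803 at 55 and 0.814 at 56 per lesion. The planned figure is reproduced, and 0.814 is the baseline below.

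**2. What alternation achieves.** Mean needle-use number over four passes with an unchanged needle:

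| Sequence | First lesion | Second lesion | Gap |
|---|---|---|---|
| A-B-A-B | (1+3)/2 = 2 | (2+4)/2 = 3 | 1 use |
| A-A-B-B | (1+2)/2 = 1.5 | (3+4)/2 = 3.5 | 2 uses |

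Alternation halves the gap but does not close it.

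**3. Bias.** Let d be the points of success lost per needle use (assumed linear) and q the share of patients with the primary lesion first. The bias in the metastatic-minus-primary difference is

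bias = d × [(1 − q) − q] = d × (1 − 2q).

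At q = 0.5 it is zero. The documents give neither d nor q, so a range is assumed: d from 3 to 10 points, q from 60% to 90%. For example, 3 × (0.4 − 0.6) = −0.6 points and 10 × (0.1 − 0.9) = −8 points.

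**4. Effect on power.** One-sided Fisher test, 56 per lesion, metastatic rate = 70% + bias, primary rate = 45%. Each cell shows the bias in points, then the power:

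| d per use | q = 60% | q = 75% | q = 90% |
|---|---|---|---|
| 3 points | −0.6; 0.795 | −1.5; 0.765 | −2.4; 0.733 |
| 5 points | −1; 0.782 | −2.5; 0.729 | −4; 0.672 |
| 10 points | −2; 0.747 | −5; 0.631 | −8; 0.504 |

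Splitting the bias between the lesions instead of charging it all to the metastasis changes these powers by about 0.001 at most.

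**5. The opposite direction.** Assume no true difference, with both rates at 57.5% (the midpoint of 45% and 70%). The unbiased rejection rate is 0.035. With 90% metastasis-first and d = 10, the bias is +8 points (61.5% against 53.5%) and the rate is 0.168. With 75% metastasis-first and d = 3, the bias is +1.5 points and the rate is 0.049.

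**6. Suction.** No arithmetic applies. The Discussion makes its statement conditional on one method, slow-pull, in both groups. Section 2.6 names two methods and states no matching rule. The condition is therefore not secured by the procedure as described.

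**The case against.** **The order problem is disclosed, with two safeguards.** This is true. The use count above applies to an unchanged needle, and a fresh needle at the right moment would narrow or reverse the gap. But the change depends on an unblinded physician sensing wear during the procedure. It does not reliably correct the gap and may itself be linked to the lesion. Disclosure stands; the conclusion that little confounding remains does not follow.

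**The size is assumed.** This is also true. A loss of 10 points per use would mean 30 points from pass 1 to pass 4 if linear, and 90% one-sided order is an extreme companion to it. The fall to 0.504 is the worst cell of the table, and most cells lose much less.

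**Stronger readings.** A reader might infer that the lesion effect is confounded, that physicians choose the order habitually, or that one needle is always reused. The text says only that the order is unspecified and that a needle change is not mandatory. A roughly even starting order would give zero expected bias even without randomisation. A reader might also take the Discussion to claim that suction cannot matter. It makes a conditional remark about omitting wet suction, and nothing suggests that the method is chosen by lesion.

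**An article condenses the protocol.** Whether pass number, needle change and suction are recorded is left to the full documents and is not criticised here.

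**Conclusion.** The point holds as openness to confounding, not as demonstrated confounding. Alternation reduces order bias without removing it, and discretionary needle change does not reliably make up the rest. Under the assumed ranges, a mostly primary-first order costs between about 2 and 31 percentage points of power (0.814 to 0.795 or 0.504). A mostly metastasis-first order raises the false-positive rate, in the most extreme case shown from 0.035 to 0.168. These figures assume linear wear, an unchanged needle, strict alternation and the plan's own independent-groups calculation. Any departure towards A-A-B-B doubles the bias.

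The suction mismatch between section 2.6 and the Discussion is a separate matter of reconciliation. Its effect on the result cannot be sized from the documents. The order question merits a change while the trial is still recruiting, because the remedy is cheap and makes the expected order bias zero.

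**What to change.** - For the remaining patients, randomise which lesion is punctured first, 1:1, where both can be approached safely. Keep the alternation, and record a reason when the allocated order is not followed.
- Reconcile section 2.6 with the Discussion so that the negative-pressure method, whichever is used, is the same for both lesions of a patient. Which method to use is not a question for this review.
- Report the primary result by starting lesion as a sensitivity analysis. This also covers patients already enrolled, if their starting lesion is known.
- In the Discussion, replace the sentence that closes the first limitation with a statement that alternation reduces order bias but does not remove it.

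The cost is a small amendment, a randomisation list and some loss of physician discretion over order. No procedure is added. The documents do not say how many patients remain to be enrolled, so the gain from randomising now cannot be quantified.

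### ROSE is optional, removes the specimen it is used on from the endpoint and may redirect later passes, with no rule that both lesions in a patient be handled alike

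*Protocol article*

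**What the plan says.** Section 2.6 of the protocol article covers ROSE for specimens from both lesion types. It says that "a portion of the specimen is cut and considered for rapid on-site evaluation (ROSE"), and then "However, ROSE is not mandatory".

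Three rules follow in the same section:

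- **Exclusion.** "When ROSE is performed, the remaining specimens are not included in the study because of the small number of specimens". The paragraph on pathology repeats this: "Specimens, excluding those from the ROSE session, are checked to determine whether they meet NOP analysis criteria".
- **Redirection.** "If malignant cells are not confirmed by ROSE, changes in the puncture site, target, and needle are considered". Carrying on as before is also allowed, since "additional puncturing, without changing the site or puncture method, is considered acceptable".
- **Stopping.** "The procedure is terminated once two specimens each are obtained from primary and metastatic lesions". The text does not say whether a specimen used for ROSE counts as one of the two.

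Section 3 concedes that the operator is unblinded: "The physician naturally knows whether to puncture the primary lesion or the metastatic lesion, which can be a confounding factor". Its limitations are puncture order, the shared needle, the suction method and the lack of blinding. ROSE is not among them.

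**The concern.** The trial is self-controlled (Section 2.2). The strength of that design is that the two results from one patient should differ only in the lesion sampled. The ROSE rules allow a second difference. An operator who knows which lesion is being punctured may check one lesion and not the other. In the checked lesion, the ROSE specimen drops out, and the passes that count may come after a change of site, target or needle prompted by a negative result. In the unchecked lesion, the counted passes had no such feedback.

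Section 3 argues that the choice of suction does not affect the primary endpoint because the same method is applied to both groups. No equal-application rule of that kind exists for ROSE.

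Section 4 says the result may change how targets for tissue acquisition are chosen. If feedback is unequal, the observed difference mixes lesion type with guided sampling. It could be too large or too small, depending on which lesion is checked more often.

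**Working it through.** **1. The plan's own figure.** Inputs from Section 2.7: 70% for metastatic lesions, 45% for primary lesions, Fisher's exact test, one-sided 0.05, power 80%, 56 patients. I treat the two lesions as independent groups of n with one result per lesion, which is the calculation that reproduces the plan's figure.

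Power = sum over all pairs (x_M, x_P) of Bin(x_M; n, p_M) × Bin(x_P; n, p_P), counting the pairs whose one-sided Fisher p-value is at most 0.05.

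- n = 54: 0.792
- n = 55: 0.803, the first n to reach 80%
- n = 56: 0.814

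The stated 56 is therefore reproduced within one patient. The ROSE point does not alter that arithmetic.

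**2. What the rules allow.**

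| Step | Lesion with ROSE | Lesion without ROSE |
|---|---|---|
| Specimen used for ROSE | Not checked against NOP criteria | None |
| After a negative ROSE | Site, target or needle may change, or may stay as they were | No feedback |
| Specimens that count | May follow feedback | Unguided |

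No sentence requires the same column for both lesions of a patient.

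**3. Size, on assumed values.** The article gives neither the frequency of ROSE nor its effect on NOP success. Let f be the net share of patients in whom ROSE favours one particular lesion, and d the gain in that lesion's success rate in those patients. The shift in that lesion's rate is s = f × d. With d = 15 points (assumed):

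- f = 10%: s = 0.10 × 15 = 1.5 points
- f = 20%: s = 0.20 × 15 = 3 points
- f = 50%: s = 0.50 × 15 = 7.5 points, which is 7.5 / 25 = 30% of the planned difference

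The formula in step 1 at n = 56 then gives:

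| Net shift s | Primary favoured, 70% vs (45% + s): power | Metastatic favoured, no true difference, (45% + s) vs 45%: rejection rate |
|---|---|---|
| 0 | 0.814 | 0.035 |
| 1.5 points | 0.766 | 0.050 |
| 3 points | 0.713 | 0.069 |
| 7.5 points | 0.528 | 0.158 |

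If the metastatic lesion is favoured and the true rates are 70% and 45%, the effect is inflated. At 7.5 points it becomes 77.5% vs 45%, and the chance of a significant result rises from 0.814 to 0.963.

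**4. Balanced use.** If unequal ROSE use is split evenly between the lesions and the gain is the same in each, both rates rise by the same amount and the average difference stays at 25 points.

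**The case against.** The strongest reply is that unequal handling is inferred from silence. Section 2.6 introduces ROSE for both lesion types, and the article condenses a longer protocol. Recording ROSE by lesion and a sensitivity analysis may well be in that protocol or in the analysis plan. This stands in part: their absence from the article is not a fault. The three rules that permit the imbalance are nevertheless stated in the article itself, and nothing there offsets them.

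A reader might infer that failed passes are discarded because they failed, so that exclusion depends on the outcome. The text does not support this. A specimen is excluded because ROSE was performed on it, whatever ROSE shows, and a good specimen is lost in the same way. Selective loss of poor passes would arise only if operators chose ROSE by how a pass looked, and the article does not say they do. What does depend on the result is redirection.

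A reader might also infer a large effect, or one that always costs power. Neither follows. Redirection is discretionary and arises only after a negative ROSE. ROSE looks for malignant cells, whereas the endpoint needs tumor cellularity of at least 20% and a tissue area of at least 4 mm². The gain in NOP success may therefore be small. Balanced use cancels on average, and use favouring the metastatic lesion raises the chance of significance.

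**Conclusion.** The concern holds in a limited form. As written, Section 2.6 allows the counted specimens of one lesion to follow cytology feedback while those of the other do not, at the choice of an operator who knows which lesion is which. That is a weakness in the stated design and more than a missing detail.

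Neither direction nor size can be derived from the document. The shifts of 1.5 to 7.5 points are assumptions about a net imbalance towards one lesion. At the low end the consequences are small: power falls by about 5 percentage points (0.814 to 0.766), and the rejection rate with no true difference stays at about the nominal 0.05. At the high end they are serious: power of 0.528, or a one-sided rejection rate of 0.158. A change is worth making because it is cheap and because imbalance cannot be assessed afterwards unless ROSE use is known for each lesion.

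**What to change.** 1. State that within a patient ROSE is handled the same way for both lesions: used on both or on neither.
2. Record, for each lesion, whether ROSE was done and whether the site, target or needle was changed as a result.
3. Repeat the primary comparison in patients without ROSE, or with the same ROSE use in both lesions. The study is ongoing, so this is useful for patients already enrolled wherever ROSE use can be established.
4. Reconcile the exclusion rule and the stopping rule in Section 2.6 by stating whether a ROSE specimen counts toward the two per lesion. If it counts, a checked lesion brings fewer than two specimens to the NOP check. If it does not, that lesion needs further passes.

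When an operator may act on a ROSE result is a procedural matter for the investigators, and no rule is proposed here.

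The cost is a short amendment, two recorded items per lesion and slightly less operator freedom. The sensitivity analysis will have fewer patients than the main analysis and so less precision. Whether extra passes arise depends on the answer to item 4.

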## 1. Introduction

In recent years, cancer genomic medicine has been implemented in clinical practice, and comprehensive genomic profiling (CGP) using next-generation sequencers (NGSs), which can detect a large number of gene sequences in tumor tissue specimens, has become available [1,2,3,4,5,6,7,8,9,10,11]. In pancreatic cancer, CGP has made it possible to select treatment options, such as molecularly targeted drugs and immune checkpoint inhibitors, that are suited to the patient, with new treatment options expected in the future [12,13,14,15,16,17,18,19,20,21]. Therefore, endoscopic ultrasound-guided tissue acquisition (EUS–TA) in unresectable pancreatic cancer requires not only a tissue diagnosis but also tissue collection in anticipation of CGP [22].

CGP systems currently approved in Japan include the OncoGuide NCC Oncopanel System (NOP; Sysmex Corporation, Hyogo, Japan) and Foundation One CDx Cancer Genome Profile (Fone; Foundation Medicine, Cambridge, MA, USA). The specimen criteria for the NOP system are tumor cellularity of ≥20% and a tissue area of ≥4 mm^2^, and that for the Fone system are tumor cellularity of ≥20% and a tissue area of ≥25 mm^2^ (Table 1).

In clinical settings, a pathologist evaluates the quality of the tissue specimen obtained by EUS–TA (during pre-check), and only cases that meet the criteria are subjected to CGP analysis (Figure 1). As pancreatic cancer is representative of low-cellularity tumors with abundant stromal components, the tumor cell content is reported to be 5–20%; accordingly, a greater amount of adequate tissue for CGP is required [23].

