The relationship between the EUS–TA technique and the percentage of successful CGP analyses has also been evaluated. Park et al. reported that the puncture needle diameter (22G or 19G) and tumor site (body–tail), but not needle type (fine needle aspiration or FNB), contributed to a successful CGP analysis of primary pancreatic specimens collected using EUS–TA [30]. Larson et al. reported that large FNB needle diameter (19G, *n* = 2; 22G, *n* = 41; and 25G, *n* = 2) was associated with a high success rate for meeting NGS analysis criteria (*p* = 0.05) [28]. Therefore, when performing EUS–TA with an FNB needle for CGP, a large puncture needle diameter, with a large amount of tissue sampled, is recommended to achieve a high analysis success rate.

However, the optimal puncture target remains controversial. Larson et al. compared the proportion of specimens that met CGP criteria between those obtained by EUS–TA for primary pancreatic lesions or percutaneous biopsies for metastatic lesions and found a significantly higher success rate for metastatic lesions than for primary lesions, despite the difference in sampling modalities (*p* = 0.036) [28]. Ikeda et al. reported that, overall, 39.2% (60/153) of pancreatic specimens obtained with an FNB needle met NOP analysis criteria during pre-check; however, primary lesion specimens (37.1%, 53/143) were significantly less likely than metastatic lesion specimens (70%, 7/10) to meet analysis criteria (*p* = 0.049) [31]. Nevertheless, data on the proportion of metastatic lesion specimens that meet CGP analysis criteria remain insufficient, and it is not yet clear whether primary or metastatic lesions have a high success rate for CGP analysis of invasive pancreatic adenocarcinoma.

Therefore, we designed a study to clarify the appropriate target for EUS–TA when CGP is planned for pancreatic ductal adenocarcinoma by comparing the success rates for meeting NOP analysis criteria between primary and metastatic lesion specimens obtained during the same EUS–TA session in patients with invasive pancreatic ductal adenocarcinoma. The protocols are described herein.

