### 2.3. Endpoints

The primary endpoint is the proportion of EUS–TA specimens obtained from primary and metastatic lesions that meet NOP analysis criteria. Although the NOP product catalog indicates tumor cellularity of ≥20% and a tissue area of ≥16 mm^2^, in actual clinical practice, a tissue area of ≥4 mm^2^ provides adequate DNA content (≥200 ng) for analysis. Thus, specimens with tumor cellularity of ≥20% and a tissue area of ≥4 mm^2^ are considered to meet NOP analysis criteria.

The secondary endpoints are as follows: rate of patients with primary or metastatic lesion specimens that meet NOP analysis criteria; technical success rates of EUS–TA with a TopGain 19G needle in primary and metastatic lesions; technical success rates of EUS–TA (regardless of needle type) in primary and metastatic lesions; adverse event rate, details, and severity; sensitivity, specificity, and accuracy of the histological differentiation of malignant and benign lesions in primary or metastatic lesion specimens; rates of successful NOP analysis of primary and metastatic lesion specimens; rate of patients who receive a drug targeting detected genetic mutations; details of genetic mutations detected upon NOP analysis; tumor cellularity and tissue area of all EUS–TA sessions; tumor cellularity and tissue area according to the nCounter system for all EUS–TA sessions; rate of patients who do not meet NOP criteria for both primary and metastatic lesion specimens and underwent liquid biopsy; rate of the necessity of percutaneous biopsy because specimens do not meet NOP analysis criteria for primary or metastatic lesions; and DNA amount in cases analyzed for DNA amount.

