### 2.7. Sample Size Determination and Statistical Analysis

The proportion of metastatic lesion specimens that meet NOP analysis criteria is expected to be approximately 70%. The proportion of primary lesions that meet NOP analysis criteria is likely to be lower than the 63.6% reported by Hisada et al. because of the reduced number of passes in the PRIMATE study. In addition, in our previous retrospective study, the proportion of primary tumor specimens obtained by EUS–TA with a 19G needle meeting criteria on pre-check was 53.8%, with a median number of punctures of four. Therefore, the proportion of primary lesion specimens that meet NOP analysis criteria in the present study is expected to be approximately 45%. Accordingly, the minimum sample size required for a Fisher’s exact test is 56 patients, assuming a one-sided significance level of 0.05 and a power of 80%. Assuming that approximately 10% of registered patients will experience difficulty in puncturing, a sample size of 61 patients is planned.

The proportion of EUS–TA specimens meeting NOP analysis criteria will be compared between primary and metastatic lesions using Fisher’s exact test. Statistical significance is set at *p* < 0.05.

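### No masking of the two endpoint pathologists to lesion origin is described, and the stated blinding limitation covers only the puncturing physician, although the readers could largely be masked

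*Protocol article*

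**What the plan says.** Section 2.3 defines the outcome: "The primary endpoint is the proportion of EUS–TA specimens obtained from primary and metastatic lesions that meet NOP analysis criteria". A specimen passes if tumor cellularity is at least 20% and tissue area at least 4 mm².

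Section 2.6 describes the reading on hematoxylin–eosin slides. "The pathological evaluation is performed by two pathologists, and any discrepancies in the measurements are resolved by discussion". On the scale, "tumor cellularity is evaluated at five levels (>80%, 60–80%, 40–60%, 20–40%, and <20"%), and area is placed in four bands. The 20% pass mark is therefore the border between the two lowest cellularity bands.

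The Discussion gives the only text on blinding: "Finally, double blinding is not possible". The reason follows: "The physician naturally knows whether to puncture the primary lesion or the metastatic lesion, which can be a confounding factor". The pathologists are not mentioned there. Neither section says whether they know which lesion a slide came from.

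The expectation has a direction. The Introduction cites a series in which "primary lesion specimens (37.1%, 53/143) were significantly less likely than metastatic lesion specimens (70%, 7/10) to meet analysis criteria". Section 2.7 plans on the same pattern: "The proportion of metastatic lesion specimens that meet NOP analysis criteria is expected to be approximately 70"%, against about 45% for primary lesions, with a one-sided 0.05 level.

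**The concern.** Who punctures and who reads are separate matters. The endoscopist cannot be masked. The pathologists largely can, and it is their grading that decides whether a specimen counts as a success. For the other limitations in the Discussion the article argues why they should matter little (alternating punctures, needle changes, the same negative-pressure method for both lesion types). For blinding it offers no safeguard, and masked reading would be the obvious one to name.

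The within-patient design removes differences between patients. It does not remove a tendency to read one lesion type more generously than the other. Such a tendency adds to the primary difference, and a larger sample would only estimate the biased difference more precisely. Settling disagreements by discussion does not protect against it if both readers share the expectation.

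The stakes are set out in the Conclusions: a higher pass rate in metastatic lesions is to lead to a recommendation of those lesions as the puncture target, possibly through guidelines.

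**Working it through.** **Inputs from section 2.7.** Pass rates 45% (primary) and 70% (metastatic), one-sided level 0.05, power 80%, Fisher's exact test, 56 patients. I take one pass/fail result per lesion type and patient, so 56 results on each side.

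**Assumed inputs.** The documents give neither a reading bias nor a within-patient correlation. I use shifts d of 0, 2, 5 and 10 percentage points in favour of metastatic specimens, and correlations φ of 0, 0.2 and 0.4.

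**Step 1: the plan's own figure.** For x primary and y metastatic passes, the one-sided Fisher p-value is the upper hypergeometric tail. Exact power is the sum over all (x, y) of Bin(x; n, 0.45) × Bin(y; n, 0.70) × 1[p(x, y) ≤ 0.05]. The smallest n with at least 80% power is 55 (80.3%), and n = 56 gives 81.4%. The stated 56 is reproduced to within one patient. Masking does not change it.

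**Step 2: error under a reading shift, independent lesions.** The true rates are set equal at p. The recorded rates are p for primary and p + d for metastatic, with n = 56 and the same sum:

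| True rate p | d = 0 | d = 2 | d = 5 | d = 10 |
|---|---|---|---|---|
| 45% | 3.5% | 5.6% | 10.2% | 23.0% |
| 57.5% | 3.5% | 5.4% | 9.8% | 22.6% |

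**Step 3: the planned Fisher test with within-patient correlation.** The probability that both lesions pass is p₁p₂ + φ√[p₁(1−p₁)p₂(1−p₂)], with p₁ = 0.45 and p₂ = 0.45 + d. There were 200,000 simulated trials per cell:

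| φ | d = 0 | d = 5 | d = 10 |
|---|---|---|---|
| 0.2 | 2.1% | 7.6% | 20.5% |
| 0.4 | 1.0% | 5.1% | 16.9% |

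Fisher's test ignores positive pairing and becomes conservative, so the absolute error is lower. The relative rise is still large.

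**Step 4: sidedness.** The analysis paragraph gives p < 0.05 without repeating that the test is one-sided. With a two-sided Fisher test at 0.05, independent lesions and p = 45%, the rejection rates are 2.9%, 5.3% and 13.2% at d = 0, 5 and 10.

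**Step 5: what a shift means in specimens.** Five points of 56 is 0.05 × 56 = 2.8 specimens, and ten points is 5.6. At a true rate of 45%, 0.55 × 56 = 30.8 metastatic specimens fail. If all failed on cellularity alone, a 5-point shift would need 2.8/30.8 = 9.1% of them to be upgraded. If only half did and the rest lacked 4 mm², it would need 2.8/15.4 = 18.2%. A change in the cellularity grade alters the result only where the area suffices.

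**The case against.** The strongest reply is that the article is silent on masking. It condenses a full protocol (version 1.2, section 2.1) that is not shown, and slide coding and reading order are details such a document may hold. This stands against the reading that the pathologists are unmasked, or that they discuss slides with the label in view. A reader might infer that, but the text neither states nor denies it. What remains is narrower: the article describes the grading in some detail and raises blinding as a limitation, yet names no safeguard and gives a reason that covers only the endoscopist.

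A reader might also infer that the Discussion wrongly declares all blinding impossible. It does not. It refers to double blinding, which is correct as written and compatible with masked readers. The sentence is incomplete, not false.

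A third tempting step starts from the Introduction, where "the tumor cell content is reported to be 5–20"%, and concludes that many primary specimens crowd the 20% mark. That is a general background figure and not a distribution of readings in this study. Section 2.7 expects about 45% of primary specimens to pass, so most specimens cannot simply follow that range.

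The size of the effect is also fairly contested. Every shift is assumed, a shift could run the other way, and at φ = 0.4 a 5-point shift leaves the planned test at about its nominal level. That the estimates are visual is inferred from the stain and the bands, because the measuring method is not named. Masking will be partial where liver or node tissue is visible on the slide. The word for discrepancies in section 2.6 may imply that each reader already scores separately, but the article does not say so.

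**Conclusion.** The point holds as an unprotected risk with a cheap remedy, not as a demonstrated bias. The primary outcome depends on graded readings with a fixed cut, prior data and planning rates favour one lesion type, and the article describes no masking of the readers.

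If the net reading tendency were 5 or 10 points towards metastatic lesions, the one-sided error of the planned test would go from 3.5% to about 10% or 23% with independent lesions. With within-patient correlation of 0.2 to 0.4 it would go from 1.0–2.1% to 5.1–7.6% or 16.9–20.5%. These figures rest on equal true rates of about 45%, 56 results per lesion type, and shifts and correlations that the documents do not supply. With no lesion-specific tendency the error stays below 5%. The sample size is unaffected.

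**What to change.** **Section 2.6.** State that the study pre-check is read on slides carrying study codes without a lesion label, presented in random order and not as primary–metastatic pairs. State that each pathologist records cellularity and area independently before any discussion, and that the discussion is held on the coded slides. If the full protocol already provides this, one sentence saying so is enough.

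**Discussion.** Say that the blinding limit applies to the endoscopist, and that masking of the readers is partial where background tissue reveals the organ. The study is ongoing, so if specimens have already been read with labels visible, report that as a limitation.

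**Cost.** Some slide handling and a few sentences of text. No additional reader, procedure or patients are needed. The gain is incomplete, because some slides will remain recognisable.
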